### Subject recruitment

Infants born in the hospital will be screened daily from 0 to 14 days of life for elevated TSB using TcB measurements, while in the hospital or, if discharged before 14 days, in the community by nurses sent out from the hospital when possible. Infants from the community will also be screened if within 14 days they choose to come to the study site for screening. The parents will be asked to return with their infants to the hospital if the parent observes new-onset jaundice between 1 and 14 days of life. If the TcB is not elevated during the first 14 days of life, the subject will cease to be eligible for the study. If the TcB is elevated and the other study inclusion and exclusion criteria are met, then the infant will be recruited for the study after informed consent in writing or thumb printing is obtained from a parent or guardian. The infant will then have a TSB measured. Enrolled infants with elevated TSB (defined as 3 mg/dl below the level recommended by the AAP
[27] to begin PT in high-risk infants) will be randomly assigned to receive FS-PT or CPT. Enrolled infants with TSB levels that are not elevated as defined above will not be treated with PT. They will continue to be screened for elevated TcB as described above. If their subsequent TcB levels are not elevated during the first 14 days of life, the infant will be withdrawn from the study.

### Subject screening

Screening criteria prior to enrolment are shown in Table 
1.

**Table 1 T1:** Screening criteria prior to enrolment

**Test**	**Screening requirement**
Gestational age and/or weight	Greater than or equal to 35 weeks gestation (or >2.2 kg if gestational age is not available). Infant must be ≤14 days old at the time of first PT.
TcB	Screened daily for the first 7 days of life if in hospital and, when possible, in the community if discharged before 7 days of life or if the patient chooses to come in for screening up to14 days of life. If the TcB is elevated (elevated will be defined as a point 3 mg/dl below that recommended by the AAP for PT in high risk infants and above) at any time during the first 14 days of life, a TSB will be done.
Physical examination (dehydration, oxygen use, ABE, life expectancy, sunburn)	Subjects cannot be dehydrated, sunburned, using oxygen, or have ABE or a life expectancy <24 hours at the time of examination by the physician for enrollment in the treatment phase of the protocol.

AAP, American Academy of Pediatrics; ABE, acute bilirubin encephalopathy; PT, phototherapy; TcB, transcutaneous bilirubin; TSB, total serum/plasma bilirubin.

### Prior and concomitant therapy

All infants who meet the AAP guideline for the initiation of PT will be treated with CPT at night or when it is not possible to use FS-PT, secondary to rain or overcast sky. CPT will be performed per hospital standards. Additionally, since the study physicians only serve as consultants for patients requiring treatment for NNJ, patient management decisions, including the need for and timing of exchange transfusion, administration of antibiotics or other testing, will be at the discretion of the attending physician. AAP guidelines will be used to direct the decision of when to perform exchange transfusion, but the final decision will be that of the attending physician. Generally, exchange transfusion is performed in any term infant in Nigeria whose TSB level is ≥20 mg/dl or in any infant with neurologic signs of ABE, regardless of the recommendations in the AAP guideline.

### Inclusion criteria

Subjects will be eligible to participate in the study if all of the following conditions exist:1) at time of birth, infant is ≥35 weeks gestation (or >2.2 kg if gestational age is not available); 2) infant is ≤14 days old at the time of enrollment; 3) at time of enrollment, infant has an elevated TcB defined as 3 mg/dl below the level recommended for high-risk infants per AAP guideline or higher; 4) parent or guardian has given consent for the infant to participate.

### Exclusion criteria

Subjects will be excluded from participation in the study if any of the following conditions exist at the time of enrollment:1) infants with a condition requiring referral for treatment not available at the hospital study site and/or CPT unit; 2) infants with a life-expectancy of <24 hours; 3) infants requiring oxygen therapy; 4) infants clinically dehydrated or sunburned; 5) infants with a temperature <35.5°C or >38°C; 6) infants with ABE on clinical examination; 7) infants meeting the criteria for exchange transfusion.

Inclusion and exclusion criteria are only applicable at the time of enrollment before randomization to prevent bias of the treatment comparison.

### Exit/discontinuation/withdrawal criteria

Subjects will exit the study (will cease to receive FS-PT or CPT) if any of the following conditions occur: 1) persistent temperature instability defined as two or more episodes of temperatures <35.0°C or >39.0°C; 2) failure to return to normothermia (defined as 35.5°C to 38.0°C) within 1 hour of being removed from PT; 3) physician treatment for dehydration or sunburn is required; 4) TSB level reaches exchange transfusion levels; 5) inter-current illness not compatible with PT or needing more care than can be provided in the FS-PT canopy or CPT ward; 6) infants requiring transfer to another hospital; 7) parent request; 8) subject death; 9) subject completes the protocol (TcB or TSB level is no longer elevated); 10) subject’s well-being, in the opinion of the Investigator, would be compromised by study continuation; 11) Institutional Review Board (IRB) recommendation; or 12) subject’s risk level indicates PT should be stopped.

Infants who have been withdrawn from the study will have a physical examination and a final TcB. Safety data will be analyzed for all days in which the subjects spend any time under either FS-PT or CPT.

Efficacy will be evaluated for all days in which the treatment was deemed safe (that is, when the infant did not have to be removed from PT due to a need for physician treatment for sunburn or dehydration, due to persistent temperature instability defined as two or more episodes of temperatures <35.0 or >39.0°C, or due to failure to return to normothermia (defined as 35.5 to 38.0°C) within 1 hour of being removed from PT).

### Randomization scheme

Enrolled infants with elevated TSB (defined as 3 mg/dl below the level recommended by the AAP to begin PT in high-risk infants) will be randomly assigned to receive FS-PT or CPT. A block randomization procedure with variable block sizes will be used to maximize unpredictability. The randomization assignments of FS-PT or CPT will be printed on sequentially numbered sheets of paper and enclosed in opaque, sealed, sequentially numbered envelopes. The sealed envelopes will be prepared independently by the study statistician based in the USA and transported to Nigeria by the regulatory sponsor. When an enrolled infant’s TSB level is obtained and found to be 3 mg/dl or more below the AAP threshold for high-risk infants the study nurse will request the next envelope. The envelope will be opened and both the envelope number and the treatment assignment will be recorded on the case report form. The laboratory technician responsible for measuring the serum bilirubin level will be unaware of the sequence of treatment allocation of either FS-PT or CPT for each eligible infant and will not be involved in administering PT. The study will not be blinded as it is not physically possible to blind either the participating infants or parents, nor the hospital personnel.

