### Study design

This is a prospective, non-blinded, single center, randomized two-stage controlled non-inferiority clinical trial. During the first stage of the study, infants will be referred from elevated transcutaneous bilirubin (TcB) screening and enrolled for the definitive TSB estimation. Only infants with significantly elevated TSB levels will qualify for inclusion into the second stage of the study for PT treatment and will be randomly assigned to receive FS-PT or CPT.

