#### Screening

During the screening period, information about the baby and the mother will be collected. TcB testing will be done for up to 14 days, using Minolta AirShields Jaundice Meter JM-103 (Draeger Medical Systems, Inc., Telford, PA, USA) either in the hospital or in the community. If the TcB is not elevated during the first 14 days of life, the subject will not be eligible for the study. If at any time during screening the infant’s TcB level rises to within 3 mg/dl below the AAP threshold
[27] for high-risk infants, inclusion/exclusion criteria will be reviewed. If the infant is eligible, the infant will be recruited for the study. The infant’s mother and/or father will be approached to ask if they are interested in participating in the research study. If they are willing, the consent form for the study will be discussed. If informed consent is given to participate, consent will be documented on the consent form in writing or thumb printing.

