#### Treatment efficacy

Efficacy will be tested by measuring TSB levels prior to the placement of the infant under PT each morning to establish baseline TSB levels. Infants with morning TSB levels that meet the criteria for PT will be randomized for FS-PT. Repeat TSB levels will be obtained at the end of each day spent under FS-PT and between ~4:00 to 5:00 pm for infants under CPT to estimate the effectiveness of the treatment for the day and to determine if the requirement for night-time PT is met.

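### The sentence that opens the randomisation envelope runs in the opposite direction to the eligibility rule, and the Treatment efficacy section words allocation as to one arm only

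*Protocol article*

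**What the plan says.** The Randomization scheme section gives two accounts of who is randomised. Its first sentence reads, in part: "Enrolled infants with elevated TSB (defined as 3 mg/dl below the level recommended by the AAP to begin PT in high-risk infants) will be randomly"; both arms are then named. Later comes the working instruction, which applies once the TSB result is available: "found to be 3 mg/dl or more below the AAP threshold for high-risk infants the study nurse will request the next envelope". Its contents are then recorded on the case report form.

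Other sections bear on the same rule:

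- Study design: "Only infants with significantly elevated TSB levels will qualify for inclusion into the second stage of the study for PT treatment".
- Subject recruitment: "Enrolled infants with TSB levels that are not elevated as defined above will not be treated with PT". Pre-treatment (stage 1) repeats that such infants do not go on to stage 2.
- Subject screening, Table 1, for TcB: "elevated will be defined as a point 3 mg/dl below that recommended by the AAP for PT in high risk infants and above".
- Inclusion criteria, item 3, for TcB: "infant has an elevated TcB defined as 3 mg/dl below the level recommended for high-risk infants per AAP guideline or higher".
- Screening, under Clinical procedures: eligibility is reviewed when the "TcB level rises to within 3 mg/dl below the AAP threshold".

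The Treatment efficacy section, after describing a baseline TSB taken before phototherapy each morning, adds: "Infants with morning TSB levels that meet the criteria for PT will be randomized for FS-PT".

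**The concern.** The trigger sentence is the only place that tells the study nurse when to draw an envelope. Its wording takes in infants whose TSB is 3 mg/dl under the AAP high-risk threshold or lower still. The rest of the protocol calls those infants not elevated and does not treat them. A reader who follows this sentence alone would randomise a different population from the one the protocol describes.

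The Treatment efficacy sentence raises a separate problem. It names one arm, ties randomisation to a morning TSB, and refers to criteria for PT without saying which. At stake are the definition of the randomised population and a clear statement of when, on what criterion and to which arms an infant is allocated.

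**Working it through.** **Trigger sentence.** Let T be the AAP phototherapy threshold for high-risk infants, in mg/dl.

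1. Literal trigger: TSB ≤ T − 3.
2. Direction given in Table 1, Inclusion criteria and Screening: level ≥ T − 3. All three state it for TcB.
3. Direction for TSB elsewhere: the abstract, Definition of high-risk threshold, Subject recruitment and the first sentence of Randomization scheme put the cut-off at T − 3 and carry the direction only through the word elevated. The trigger is therefore the only sentence that attaches an explicit direction to TSB, and it points away from that word.
4. Overlap of (1) and (2), applied to the same measurement: TSB = T − 3 exactly, and nothing else.
5. Consequence of (1) alongside the other sections: an envelope would be opened for an infant whom Subject recruitment and Pre-treatment (stage 1) bar from study phototherapy. The two instructions cannot both be followed.

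**Illustrative size.** The input is from Sample size: in year 1 of the observational study, 66% of 826 infants referred for elevated TcB had significantly elevated TSB.

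- Elevated: 0.66 × 826 = 545.2, about 545 infants.
- Not elevated: 0.34 × 826 = 280.8, about 281 infants.

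The literal trigger would select roughly the 281 and leave out the 545, apart from any infant at exactly T − 3.

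**Does any planned number depend on the trigger?** The inputs from Sample size are 80% efficacy in both arms, a 10% margin, one-sided alpha 0.025 and 80% power.

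- Per group: (1.96 + 0.8416)² × (0.8 × 0.2 + 0.8 × 0.2) / 0.10² = 7.849 × 32 = 251.2, rounded up to 252. The total is 504, as stated.
- Safe-day allowance: 504 / 0.90 = 560, as stated.
- Loss allowance: 560 × 1.10 = 616, as stated.
- Stage 1: 616 / 0.66 = 933, against a stated 915 or more, a gap of about 2%.

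None of these uses the direction of the trigger, so none changes when it is reconciled.

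**Treatment efficacy sentence.** Set against the other sections:

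- *Arms.* It names FS-PT only. Study design, Subject recruitment, Randomization scheme and Pre-treatment (stage 1) all say FS-PT or CPT.
- *Criterion.* Criteria for PT could mean the study cut-off (T − 3) or the AAP guideline for starting phototherapy, which Prior and concomitant therapy, Pre-treatment and Treatment (stage 2) use for CPT at night or in poor weather. If both refer to the high-risk line, the two readings differ by 3 mg/dl.
- *Timing.* It follows a sentence about measurement each morning and does not say that allocation happens once.

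**The case against.** The strongest reply is that nobody reading the whole protocol could mistake the rule. The same section opens by randomising elevated TSB, Study design restricts stage 2 to such infants, and two sections bar the others from phototherapy. The trigger is then a slip of phrasing. Most of this stands: the intended direction is clear, and nothing in the document shows that any infant was wrongly randomised. It does not remove the point, because the slip is in the instruction acted on at allocation. It is also fair that the explicit upward wording concerns TcB, so it supports the TSB direction only by analogy.

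Two stronger readings are tempting, and the document does not support either.

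*Daily re-randomisation.* A reader might infer it from the Treatment efficacy sentence, the more so because efficacy is judged per treatment day and the abstract counts 616 days where Sample size counts 616 infants. But Data collection and analysis bases intent-to-treat on each enrolled infant's assignment and defines per-protocol across all of an infant's treatment days. Sample size counts 308 infants in each group. The sentence after the disputed one mentions infants under CPT. Repeated allocation is a possible misreading, not a stated procedure.

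*Bias towards non-inferiority.* A reader might argue that less jaundiced infants would succeed under either treatment and so bring the arms together. The primary outcome is a rate of change in TSB, not its level, and nothing in the document links a lower starting TSB to success on it.

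**Conclusion.** The point holds as an internal contradiction in the allocation instruction. The trigger sentence, read literally, selects the complement of the group described everywhere else, with overlap at a single value. The Treatment efficacy sentence separately conflicts with two-arm allocation and leaves criterion and timing unclear; it does not itself select non-elevated infants.

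The 34% against 66% split is illustrative only. It assumes that the trial's referrals resemble those of the earlier observational study and that the sentence is followed to the letter. It is not an estimate of misallocated infants or of bias. The sample size is unaffected. No view is taken on which bilirubin level is clinically right. The contradiction should be corrected, but it does not undermine the design.

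**What to change.** - In Randomization scheme, reconcile the trigger sentence with the eligibility definition in Study design, Subject recruitment, Table 1, Inclusion criteria and Pre-treatment (stage 1), so that one definition opens the envelope. State its direction explicitly for TSB, not only for TcB.
- Check that the working instruction held by the study nurses matches. Trial status reports recruitment under way, so this check should come first.
- In Treatment efficacy, say that each eligible infant is allocated once, to FS-PT or CPT, name the criterion used, and say that intent-to-treat follows that allocation. This concerns the assignment, not every hour of treatment received: CPT at night or in poor weather continues as the protocol already describes, and the planned as-treated analysis is untouched.

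The cost is two reworded sentences and one check of site instructions. No sample size, margin or analysis changes.

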### Laboratory testing procedures

#### *G*lucose-6-phosphate dehydrogenase

Because of the high prevalence of G6PD deficiency in our study population, enrolled infants will be routinely screened for this condition using simple and inexpensive supplies. The method will be based on the fluorescent blood spot originally developed by Beutler and colleagues
[29]. This test has been considered a standard method of G6PD screening especially in resource-poor settings, since inexpensive reagents and materials can be used.

#### Bilirubin

TSB will be estimated using standard methods. Hematocrit testing will be done using standard laboratory methods.

#### Coombs testing and blood typing

Coombs testing and blood typing will be performed in the blood bank laboratory at IMH.

#### Specimen collection

Blood specimens for TSB measurements will generally be collected by heel-stick. Specimens for G6PD, blood type and Rh will be drawn by venipuncture.

### Clinical procedures

#### Criteria for admission

Infants born in the hospital will be screened daily from 0 to 14 days of life for elevated TcB while in the hospital or, if discharged before 14 days, in the community by nurses sent out from the hospital when possible. Infants ≤14 days old from the community presenting to the study site will also be screened. The parents will be asked to return with their infant to the hospital if the parent observes new onset jaundice between 1 and 14 days of life.

#### Screening

During the screening period, information about the baby and the mother will be collected. TcB testing will be done for up to 14 days, using Minolta AirShields Jaundice Meter JM-103 (Draeger Medical Systems, Inc., Telford, PA, USA) either in the hospital or in the community. If the TcB is not elevated during the first 14 days of life, the subject will not be eligible for the study. If at any time during screening the infant’s TcB level rises to within 3 mg/dl below the AAP threshold
[27] for high-risk infants, inclusion/exclusion criteria will be reviewed. If the infant is eligible, the infant will be recruited for the study. The infant’s mother and/or father will be approached to ask if they are interested in participating in the research study. If they are willing, the consent form for the study will be discussed. If informed consent is given to participate, consent will be documented on the consent form in writing or thumb printing.

#### Pre-treatment (stage 1)

The enrolled infant will then have a TSB drawn (stage 1) using the Advanced Bilirubinometer Stat-Analyzer, Model BR2 (Advanced Instruments, Inc, Norwood, MA, USA) before treatment (stage 2). Enrolled infants with elevated TSB qualify for inclusion into the second stage of the study and will be randomly assigned to receive FS-PT or CPT. Enrolled infants with TSB levels that are not elevated as defined above will not proceed to the second stage to be treated with PT. However, they will continue to be screened for elevated TcB as described above. If their subsequent TcB levels are not elevated during the first 14 days of life, the infant will be withdrawn from the study. All infants who meet the AAP guideline for the initiation of PT will be treated with CPT at night or when it is not possible to use FS-PT, secondary to rain or excessive cloud cover (defined as cloud cover persisting for more than 2 hours). FS-PT will be optimized in all infants by using white cloth lining the bottom and sides of the cot and exposing the infant maximally. CPT will be performed per international standards of practice
[27].

#### Treatment (stage 2)

FS-PT will be started in the morning after the irradiance level inside the canopy is at least 8 μW/cm^2^/nm, and will be stopped in the late afternoon when the irradiance level drops below 8 μW/cm^2^/nm or at any point during the day during a rainy/cloudy day when the irradiance stays below 8 μW/cm^2^/nm. If the irradiance persists below 8 μW/cm^2^/nm for more than 1 hour and the infant qualifies for PT per the AAP guideline, CPT will be initiated. If the irradiance again exceeds 8 μW/cm^2^/nm then the infant may again be placed in FS-PT.

#### Treatment canopies

Two FS-PT canopies will be used: one fitted with the Gila Titanium film and the other fitted with the Air Blue 80 film because of concerns about irradiance and heat. The Titanium canopy transmits approximately 33% blue light in the wavelength range 400 to 520 nm with much lower heat and will be used during sunny periods of the day. The Air Blue canopy transmits roughly 79% blue light as well as heat and will be used during cooler overcast periods of the day. The infants will be moved from one canopy to the other as needed during the day, when the weather changes, with the goal of keeping the irradiance level above 8 μW/cm^2^/nm. The irradiance will be measured at an infant’s abdomen level with a Bili-Blanket Meter II every half hour in infants under FS-PT (if possible, additional measurements may be done) and daily in those infants under CPT.

The proportion of blue light accessible to the subjects under FS-PT canopies is dependent on the location of treatment canopies in relation to surrounding buildings. It is therefore imperative that the treatment canopies be placed in a location with proven day-long sun exposure throughout the year, preferably one also protected from potentially violent wind currents and surface dust generated by traffic. In fact, the single most important reason for replacing films is wind damage. A roof top terrace, presently in use in our study, has proven to be a very satisfactory location. A courtyard of adequate size surrounded by low buildings could be even more suitable. Finally, perhaps most ideal and practical, will be the construction of a suitable FS-PT room or a small permanent building with a glass or plexiglass roof, in an appropriately “sunny” part of a hospital. This would be a most ideal solution to prevent issues with wind, dust, security, and so forth. However, such a treatment facility may overtax local resources.

